#### **6.5.2 POST-TREATMENT ASSESSMENT**

The post-treatment assessment is conducted face-to-face at the clinic, or video if the family cannot travel to the clinic or prefer so. Adolescent and caregiver-reported questionnaires are answered online directly to our trial database BASS. See **Table 2** for information regarding which measures are administered at this time point. The post-treatment assessment is planned to occur as quickly as possible after the end of the 10-week treatment, and never later than 2 months after the treatment.

#### **6.5.3 FOLLOW-UP ASSESSMENTS**

Follow-ups will be administered 3 and 12 months after the end of the 10-week I-BA treatment period, or 11 weeks from when the referral is sent for TAU. As with the post-treatment assessment, these assessments are conducted face-to-face at the clinic or over video. The CDRS-R interview will be audio-recorded. Adolescent- and caregiver-reported questionnaires are answered online directly to our trial database BASS, preferably prior to the face-to-face assessment. See **Table 2** for information regarding which measures are administered at each time point. For these follow-ups, there is a -1 month/+2-month time period for data collection. After completing the three-month follow-up, participants are given a gift card worth 400 SEK.

**Table 2. Assessments points for each measure**

| Assessment points
Outcomes         | Baseline | Weekly during treatment | Post-treatment | 3-month follow-up
(primary endpoint) | 12-month follow-up |
|---------------------------------------|----------|-------------------------|----------------|-----------------------------------------|--------------------|
| Baseline measures              |          |                         |                |                                         |                    |
| Demographic data (clinician)          | X        |                         |                |                                         |                    |
| Demographic data (caregiver)          | X        |                         |                |                                         |                    |
| MINI-KID                              | X        |                         |                |                                         |                    |
| DSHI                                  | X        |                         |                |                                         |                    |
| Clinician-rated                |          |                         |                |                                         |                    |
| BASS platform usage data + phone time |          |                         | X              |                                         |                    |
| Blindness checks                      |          |                         | X              | X                                       | X                  |
| CDRS-R                                | X        |                         | X              | X                                       | X                  |
| CGI-S                                 | X        |                         | X              | X                                       | X                  |
| CGI-I                                 |          |                         | X              | X                                       | X                  |
| CGAS                                  | X        |                         | X              | X                                       | X                  |
| iPAS                                  |          |                         | X              |                                         |                    |
| Child-reported                 |          |                         |                |                                         |                    |
| QIDS-A 17                  | X        | X                       | X              | X                                       | X                  |
| ARI                                   | X        |                         | X              | X                                       | X                  |
| ASA                                   | X        |                         | X              | X                                       | X                  |
| BADS                                  | X        | X                       | X              | X                                       | X                  |
| Concomitant interventions             |          |                         | X              | X                                       | X                  |
| CSQ                                   |          |                         | X              |                                         |                    |
| ISI                                   | X        |                         | X              | X                                       | X                  |
| KIDSCREEN-10                          | X        |                         | X              | X                                       | X                  |
| Need for further treatment            |          |                         |                | X                                       |                    |
| NEQ                                   |          |                         | X              | X                                       |                    |
| RCADS-S                               | X        |                         | X              | X                                       | X                  |
| Treatment credibility                 |          | X (week 3)              |                |                                         |                    |
| WSAS                                  | X        |                         | X              | X                                       | X                  |
| Caregiver-reported             |          |                         |                |                                         |                    |
| QIDS-A 17                  | X        | After 5 weeks           | X              | X                                       | X                  |
| Concomitant interventions             |          |                         | X              | X                                       | X                  |
| CSQ                                   |          |                         | X              |                                         |                    |
| EEAC                                  | X        |                         | X              | X                                       | X                  |
| KIDSCREEN                             | X        |                         | X              | X                                       | X                  |
| Need for further treatment            |          |                         |                | X                                       |                    |
| NEQ                                   |          |                         | X              | X                                       |                    |
| RCADS-S                               | X        |                         | X              | X                                       | X                  |
| TIC-P                                 | X        |                         | X              | X                                       | X                  |
| Treatment credibility                 |          | After 3 weeks           |                |                                         |                    |
| WSAS                                  | X        |                         | X              | X                                       | X                  |

**Note:** For full names of measures, see section 5.7.

## **6.6 END OF TRIAL**

The trial will end when the final data (at the 12-month follow-up) has been collected for the final participant.

### **6.6.1 PARTICIPANT WITHDRAWAL FROM TRIAL**

Participants are free to withdraw from the trial at any point. After the withdrawal, participants will not be requested to complete any further measures but will be asked to provide non-obligatory feedback regarding their reason for withdrawal. This reason (if given) will be logged for reporting purposes. Once participants have withdrawn from the trial, it will not be possible to re-enter or resume treatment. Withdrawn participants will not be replaced in the trial.

### **6.6.2 DISCONTINUATION OF TRIAL**

Outcome measures will not be analyzed until all data from the primary endpoint is collected and will therefore not inform decisions to stop the research. However, serious adverse events (see section 9.1 for definitions) will be reviewed, and if there is any indication that these are linked to the intervention consideration will be given to discontinuing the trial on the advice of the research group and trial Sponsor. Failure to recruit could also be a reason to stop the trial.

### **6.6.3 CONCOMITANT INTERVENTIONS**

Any medication for the indication of depression (primarily antidepressants), ADHD (primarily central stimulants), and neuroleptics is required to have been stable for the last six weeks prior to inclusion in the trial. Additionally, participants in the I-BA groups are encouraged (if possible, according to her/his treating clinician) not to alter her/his medication until after the 3-month follow-up. Participants must not have received previous evidence-based psychological treatment (CBT or IPT) or BA for depression within 12 months prior to inclusion into the trial. Further, the participants in the ICBT groups are asked to not start any parallel psychological treatment until after the 3-month follow-up. Data on the use of medication and psychological interventions are collected at each assessment point. Any deviations to protocol will be noted and potentially considered in the statistical analysis.

## **6.7. QUALITY CONTROL**

The trial will be conducted according to good clinical practice principles (GCP). Data quality and safety aspects will be regularly monitored by an independent party, the Karolinska Trial Alliance (KTA). Statistical analyses will be conducted under the guidance of the Karolinska Institutet Biostatistics Core Facility ([www.biostatcore.ki.se](http://www.biostatcore.ki.se)).

## **7 DATA MANAGEMENT**

All aspects of data management of the trial will comply with the General Data Protection Regulation (GDPR) and good clinical practice (GCP). Notes will be made in the medical record software Take Care (included participants only) according to BUP Stockholm standard routines for research trials on internet-delivered treatment.

### **7.1 DATA COLLECTION AND HANDLING**

Data will be collected both manually (paper Case Report Forms (CRFs)) and digitally (adolescent- and caregiver-reported questionnaires completed via the internet directly into the trial database BASS). Some data will also be extracted digitally from the treatment platform, and then entered to BASS.

The CRFs will not bear the participant's name, instead the trial identification number will be used for identification. CRFs will be stored securely in a locked file cabinet. Data from the CRFs will consecutively be entered manually into BASS by a member of the research team. The delegation log will identify all those personnel with responsibilities for data collection and handling, including those who have access to the trial database. Audio- and video recordings of assessments will be stored on an external hard drive in a locked file cabinet. The recordings will be used for methodology checks, re-ratings if blinding is broken and future training of trial assessors.

#### **7.1.1 BASS**

BASS is the name of the treatment platform and trial online database. BASS is used both for manual entry of clinician assessed/gathered information, as well as for digital administration of written consent as well as adolescent- and caregiver-reported questionnaires. Regardless of the method above, all data goes into the same database. BASS has a fine-grained privilege-system which ensures that personnel only can view information and edit settings that pertain to their role in the research project, including only viewing their relevant participants. All data sent between the platforms and the user are encrypted using a 2048-bit SSL certificate. The system is setup so that only a port 80 and 443 is visible on the internet to the public.

The BASS system store names of participants and telephone numbers (for the use of sending SMS). Logging into the BASS platform requires username, password, and a temporary code sent by SMS (i.e., two-factor authentication which is required for systems storing sensitive data). Once the trial is finished, names and telephone numbers will be removed from BASS.

When the trial has ended, data will be extracted from BASS by the trial coordinator ([name]), then properly prepared (by a member of the research team, including adding a variable for the treatment allocation), and then securely transferred to the parts responsible for statistical analyses (see section 8). Some analyses will also be made locally by the research team.

### 7.1.2 TEAMS

Teams is the software solution that will be used for the videoconference assessments. Teams can be used in the common modern browsers (e.g., Chrome, Safari and Firefox), as well as an external application. Through Teams, an e-mail is sent from the research team with a link from where the participant initiates the video conference. Teams offers password-protected meetings, a lobby function and end-to-end crypton.

## 8 STATISTICAL ANALYSIS

**Analysis of trial feasibility:** Descriptive statistics on trial feasibility data, e.g., number of excluded patients and reasons to exclude, participant refusals and causes for refusal (e.g., did not want to be randomised to TAU), withdrawal, and attrition rates, and number of patients who declined to participate and reasons why.

**Summary of baseline data:** All baseline variables will be summarized by randomised group.

**Analysis of acceptability of guided and self-guided I-BA:** Descriptive statistics on treatment satisfaction, treatment credibility and therapist time.

**Analysis of clinical efficacy:** We will follow the CONSORT guidelines in reporting and analyzing our data. The quantitative analyses of continuous measures (primary and secondary outcomes) are conducted according to the “intent-to-treat” principle, including all randomised participants in hierarchical linear mixed-models analysis. Linear mixed models are also an adequate method to handle missing data. Cost data will include resource use costs (e.g., hospital visits, medication and absence from school, caregiver’s absence from work) and cost of I-BA or TAU. Cost differences between guided I-BA, self-guided I-BA and TAU can be calculated, as well as the incremental cost effectiveness ratio (ICER). The ICER is a global estimate of cost-effectiveness and represents the additional cost that is associated with the additional clinical effect in one intervention compared with another.

## 9 RECORDING AND REPORTING OF ADVERSE EVENTS AND REACTIONS

### 9.1 DEFINITIONS

**Table 3.** Definitions of adverse and serious adverse events relevant for this trial (60)

| Term                        | Definition                                                                                                                                                                                                                                                                                                                                                                                                                                         |
|-----------------------------|----------------------------------------------------------------------------------------------------------------------------------------------------------------------------------------------------------------------------------------------------------------------------------------------------------------------------------------------------------------------------------------------------------------------------------------------------|
| Adverse Events (AE)         | Side effects that are harmful. Not necessarily a causal relationship with the treatment. For example: 

- a psychological event (e.g., depressed mood).

- an increase in the severity or frequency of a pre-existing symptom or condition (e.g., increased self-injury)

                                                                                                                      |
| Serious Adverse Event (SAE) | Any untoward medical occurrence that: 

- results in death (e.g., suicide)

- is life-threatening (e.g., suicide attempt)

- requires hospitalization or prolongation of existing hospitalization (e.g., due to high suicide risk)

- results in persistent or significant disability or incapacity

- is otherwise considered medically significant by the investigator

 |

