### **5.5.2 EXCLUSION CRITERIA**

- 1) Immediate risk to self or others, requiring urgent medical attention, such as suicidality, or repeated self-injurious behavior.
  - Confirmed by the assessor at the telephone screening or/and face-to-face inclusion assessment, with the help of a structured clinical interview and a screening instrument for assessing non-suicidal self-harm inventory (DSHI-7).
- 2) Other psychiatric disorders or social problems requiring other actions at first hand (e.g., diagnosis of organic brain disorder, intellectual disability, psychosis, bipolar disorder, eating disorder, or alcohol/substance dependence; ongoing bullying in school, abuse and/or neglect in the family; high and prolonged absence from school).

- Confirmed by the assessor at the telephone screening or/and face-to-face inclusion assessment, with help of the clinical interview and information from the caregiver and the adolescent.
- 3) Previous psychological treatment for MDD for a minimum of at least 3 sessions within the last 12 months prior to assessment.
  - Confirmed by the caregiver at the telephone screening or/and face-to-face or inclusion assessment.
- 4) Current use of benzodiazepines.
  - Confirmed by the caregiver at the telephone screening or/and face-to-face or inclusion assessment.
- 5) Ongoing psychological treatment for any other psychiatric disorder.
  - Confirmed by the caregiver at the telephone screening and/or face-to-face inclusion assessment.

Excluded families will be directed to other more suitable treatment options.

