#### ***The Deliberate Self Harm Inventory for youths – (DSHI-Y-7)***

The 7-item DSHI for youths that will be used to assess presence and frequency of non-suicidal self-injury, to help the clinician decide on inclusion/exclusion. The DSHI-Y-7 is adapted for adolescents from the DSHI-17 (30), an empirically supported measure of various aspects of NSSI originally developed for use with adults. The DSHI-17 has demonstrated good test-retest reliability and adequate concurrent validity among adolescents (30).

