#### **9.4 HANDLING OF ADVERSE EVENTS**

Adverse events will be noted by the trial coordinator in a specific log (including date, recorded clinical symptoms, and a brief description of the event). The research team could be notified about adverse events in numerous ways, including through direct (text or telephone) communication with the participant, or at follow-up assessments. Regular meetings (treatment conferences) will be held within the research team where treatment progress and potential adverse events are discussed. Cut-off scores on the suicidal item in QIDS-A17 (self-rated depressive symptoms), might also be indicators of adverse events, and thus be registered in the AE-log. Scores of 2 or 3 points on the suicide item corresponding to a yes to “I think of suicide or death several times a week for several minutes” or “I think of suicide or death several times a day in some detail, or I have made specific plans for suicide or have actually tried to take my life”, will automatically raise a flag in the BASS system, to directly notify members of the research team to follow this up (via the telephone) with the participant.

SAEs will be recorded in the patient’s medical record (Take Care), as well as in the trial coordinator’s log. Appropriate action will be taken in the case of SAE, making sure the participant will get in contact with suitable health care services. Events will be considered as potentially treatment-related up to the 3-month follow-up, where the reporting of adverse events will terminate. The PI will immediately notify the Sponsor of any events of SAE. The PI and sponsor will work together to identify the extent of the SAE and to determine what urgent safety measures are required.

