## **12 ETHICAL CONSIDERATIONS**

ICBT differs from face-to-face therapy only in the format and mode of delivery, but still contains the same evidence-based ingredients and principles as recommended in guidelines for depression. ICBT for depression has good empirical support for adults, and our assumption is that it is likely useful and effective for adolescents as well.

Verbal information about the study and written informed consent forms will be provided to the adolescent and both caregivers prior to baseline assessment. All participant families will be volunteers, competent to provide informed consent. Participants may withdraw from the trial at any time.

Depression is a high-risk group to work with and patient safety will be a high priority in this study. Participants in all treatment arms will answer brief measures of depression weekly during the intervention, allowing depressive symptoms and suicidal ideation to be monitored. A thorough diagnostic and mental health status examination before enrolment of participants will prevent patients with more immediate needs or risks from being included in the study and offered alternative treatment.

The treatment target of the I-BA-interventions is to decrease depressive symptoms and increase daily functioning through behavior change. Therefore, we expect commonly experienced negative treatment effects for some participants, such as occasional discomfort due to approaching previously avoided and difficult situations, occasional stress due to tempo and workload in treatment, and at times feeling worse while processing treatment content. The treatment model encourages the patients to approach situations that may evoke temporary discomfort, e.g., reconnect with a friend that you have not spoken to in a while. A thorough rationale will be given for each component of the treatment as to prepare the participant for the expected temporary discomfort and other prerequisites of the treatment. Behavior change will also happen in small steps, in accordance with the values and goals of the adolescent.

This study will be conducted within regular health care, which means that the project will use medical records and be able to quickly refer adolescents in need of more help. We will also have weekly conferences discussing patients and a child- and adolescent psychiatrist will be present at these conferences.

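### Increased self-injury is the protocol's own example of an adverse event, but it is measured only at baseline and later captured by unstructured report with unequal contact between arms

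*Protocol*

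**What the plan says.** Table 3 in section 9.1 gives as an example of an adverse event "an increase in the severity or frequency of a pre-existing symptom or condition (e.g., increased self-injury").

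Section 5.7.1 says that the DSHI-Y-7 "will be used to assess presence and frequency of non-suicidal self-injury, to help the clinician decide on inclusion/exclusion". Section 5.7 refers to Table 2 for the timing of every measure, and Table 2 marks the DSHI at baseline only.

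Exclusion criterion 1 in section 5.5.2 is "Immediate risk to self or others, requiring urgent medical attention, such as suicidality, or repeated self-injurious behavior". Self-injury below that level is not named as an exclusion.

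On how events become known, section 9.4 says that trial staff "could be notified about adverse events in numerous ways, including through direct (text or telephone) communication with the participant, or at follow-up assessments". It adds regular team meetings and an automatic flag on the QIDS-A17 suicide item. High scores on that item "might also be indicators of adverse events, and thus be registered in the AE-log". Section 12 applies the weekly form to every arm: "Participants in all treatment arms will answer brief measures of depression weekly during the intervention". Section 12 also promises careful adverse event monitoring in all three groups, while section 9.2 gives close monitoring to the therapist. Adverse event reporting ends at the 3-month follow-up (section 9.4).

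**The concern.** An increase in frequency or severity is a statement about two values, one before and one after. The protocol takes the first on a scale designed for the purpose and schedules no second. Adolescents with some self-injury may be enrolled, so for them the baseline is not zero and a worsening is a real possibility.

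The interest is greatest for self-guided I-BA. The rationale in section 3 asks whether therapist support can be left out without loss of efficacy or safety. Self-injury is a harm that the protocol itself names. If it is more likely to be reported where a therapist is in regular contact, the self-guided arm could look safer than it is.

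**Working it through.** No arithmetic in the protocol bears on this point. The check sets the schedule, the reporting routes and the contact by arm side by side.

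1. **Scheduled self-injury measurements (Table 2).** DSHI: baseline 1, weekly 0, post-treatment 0, 3 months 0, 12 months 0. That is 0 of 3 post-baseline visits. A change for participant *i* is d_i = y_i(later) − y_i(baseline). The first term is never scheduled, so neither d_i nor its comparison between arms can be formed on this scale.

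2. **Other structured sources after baseline.** The QIDS-A17 is answered weekly in all arms, but the two answers quoted in section 9.4 as raising the flag concern thoughts of suicide or death, plans and attempts. Neither mentions non-suicidal self-injury. The NEQ-20 (section 5.7.4; post-treatment and 3 months) ends with an open question on other negative events, so self-injury can be volunteered there but is not described as being asked about. The protocol does not say whether the CDRS-R interview covers self-injury, so nothing is rested on that either way.

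3. **Unstructured sources.** Messages, calls, follow-up assessments and team meetings (section 9.4). Section 9.4 names no self-injury question to be put at any of these.

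4. **Contact by arm.**
   - Guided I-BA: a trial therapist who logs in at least every 48 hours, with contact typically several times weekly (section 6.4.1).
   - Self-guided I-BA: the same programme without therapist support (section 6.4.1).
   - TAU: referred to local CAMHS or primary care units (section 6.4.2), so no trial therapist.
   - Same in all arms: the weekly QIDS-A17, the flag and resulting call, and the blinded assessments.

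5. **Consequence.** Let λ be the true rate of increased self-injury in an arm and p the probability that a case reaches the log. The logged rate is λ × p. For guided (G) against self-guided (S), the ratio of logged rates is (λ_G × p_G) / (λ_S × p_S). With equal true rates this becomes p_G / p_S, which is 1 only if reporting is equally likely in both arms. Step 4 gives reason to expect p_G > p_S, so the tendency is towards more logged events in the guided arm. The protocol gives no figure for either p, so the size is unknown.

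**The case against.** The case on the other side is substantial.

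- **Cases can be found.** A reader might infer that a rise in self-injury cannot be detected, or that Table 3 cannot be applied. The protocol does not support that. A participant or caregiver can report it by message, call, interview or the NEQ-20 open question, and a call after a QIDS-A17 flag may bring it out. An event so reported meets Table 3 and can be tabulated by arm. For the same reason it cannot be said that few or no such events will be reported.
- **An adverse event definition is not an outcome scale.** Table 3 gives general examples, and section 9 requires no score before and after. Headache and fatigue are expected events in section 9.2 with no instrument of their own in Table 2. This stands: there is no formal contradiction between the sections.
- **Baseline-only use fits the stated purpose.** The DSHI-Y-7 is there for eligibility, and the objectives in section 4.1 contain no comparison of safety between arms. This also stands. The remark on safety in section 3 is background and not an objective.

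What these arguments leave untouched is the quality of the later information. It depends on someone raising the matter, and the opportunity to do so differs by arm. The promise of monitoring in all three groups does not remove that difference while close monitoring is assigned to a therapist whom only one arm has.

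**Conclusion.** The concern holds as a weakness of safety ascertainment. After baseline, self-injury is captured only by unstructured report with probably unequal opportunity between arms. Change from baseline and differences between arms therefore cannot be measured reliably, and logged counts should not be read as incidence.

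The schedule part is certain: 0 of 3 post-baseline visits carry the measure. The unequal reporting is an inference from unequal therapist contact. Its direction is plausible but not established, because assessments and weekly forms are the same in all arms. The number of participants affected cannot be given, since the protocol states no frequency of self-injury at entry. The primary CDRS-R analysis is not touched.

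**What to change.** In Table 2, add the DSHI-Y-7 at post-treatment and at the 3-month follow-up, completed online in BASS and given in the same way in all three arms. These are the two visits within the adverse event reporting period. Report the results by arm as a descriptive safety outcome.

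Use the same recall period as at baseline, or convert frequencies to a common time unit. The protocol does not state the baseline period, so the amendment should. Asking about the time since the last contact would not do. The 3-month visit has a window of −1 to +2 months (section 6.5.3), so it falls 3 − 1 = 2 to 3 + 2 = 5 months after treatment ends. A constant monthly rate counted from the end of treatment could then give totals differing by a factor of 5/2 = 2.5.

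For participants already past these visits, state that self-injury was captured by spontaneous report and that arm comparisons are limited. This may concern many: version 1.5 dates from October 2023, while section 6.1 planned recruitment across Christmas 2021 and summer 2022.

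The cost is an amendment and one 7-item form at each of two visits. Nine adolescent measures are common to both (QIDS-A17, ARI, ASA, BADS, concomitant interventions, ISI, KIDSCREEN-10, RCADS-S, WSAS). The NEQ makes 10, and the CSQ (post-treatment) or need for further treatment (3 months) makes 11, so each visit would go from 11 to 12. If the change comes late, the data will be partial.
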